##### Consensus Criteria

Delphi studies lack consensus on the specific threshold for agreement. Significantly, Linstone and Turoff [133] posit that an agreement of >80% is neither the central objective of the Delphi process nor always practically possible. In this study, items rated as “essential” or “very important” by ≥75% will qualify for inclusion, whereas those judged as “unimportant” or “not at all important” by ≥75% will qualify for exclusion. Items not fulfilling these criteria will be defined as not having reached a consensus. This threshold value [134,135] is situated between the 50% consensus supported by some [136,137] and the 100% cutoff point suggested by others [138]. Consensus criteria will be applied after the consensus meeting.

To gain additional insights into the perspectives of the 3 stakeholder groups, comparative statistics will be calculated after each round for review by the core study team. The parametric 1-way ANOVA will be used to investigate differences in stakeholder responses during each round if the assumptions of normal distribution and homoscedasticity are met [139]. These will be inspected using histograms and the Shapiro-Wilk test and the Levene test for equality of variances, respectively. Statistically significant results will be investigated using post hoc analyses to be chosen in accordance with whether homoscedasticity is met [140]. In the event of violations of the assumptions of normality, the Kruskal-Wallis *H* test, a nonparametric alternative, will be used as it is predicated on rank-based assessment and does not presuppose normality or homogeneity of variance [141]. Moreover, in the event that we are unable to identify sufficient carers to complete the Delphi survey, we will use the independent-sample 2-tailed *t* test to investigate statistically significant differences between HCPs and people with DCM. If the assumptions for the test are not met, we will use its nonparametric equivalent, the Mann-Whitney *U* test. Significance will be assumed at *P*<.05.

#### Consensus Meeting

The consensus meeting via Google Meet (Google LLC) will be attended by a maximum of 20 randomly selected HCPs, people with DCM, and carers who have completed both rounds of the Delphi survey, preserving the key stakeholder and geographical representation previously described. Participants will be presented with round 2 voting results, as previously described, and asked to anonymously rate the importance of each item for a final time using the polling tool. Frequency percentages will be generated in real time and presented to the voters on-screen to facilitate discussion. The facilitator will guide further discussion regarding any items garnering equal consensus (50%) between the agreement (“essential” and “very important”) and disagreement (“unimportant” and “not at all important”) before asking participants to vote again. In all other cases, items failing to meet the predetermined ≥75% consensus score will be eliminated.

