#### Expert Selection

The sample composition significantly determines the validity of the study results [103,104]; therefore, an element of careful judgment is warranted to ensure a “balanced” panel [104-106]. To ensure a judicious selection of experts, this study will use a purposive sampling approach, drawing surgeons, other HCPs, and people with DCM as participants from the specialized RECODE-DCM community. People with DCM will be considered if they (1) have been formally diagnosed with DCM and are at least 6 months after surgical decompressive treatment, the time point at which neurological recovery is considered to halt for most [107], or (2) have undergone at least 6 months of nonoperative management [49]. Professional stakeholders will be invited to participate if they (1) are experienced in managing DCM for at least 5 years; (2) belong to key clinical disciplines, including spinal surgery, neurology, combined physical and psychological rehabilitation medicine, physiotherapy, pain management, and primary care [4,108]; and (3) have no conflict of interest in developing a CIS. All participants will be English-speaking adults (aged ≥18 years).

A diverse and geographically representative panel will be sought, in keeping with the aim of developing an internationally suitable CIS. Adequate patient involvement is vital to this endeavor to help foster evidence-based decision-making [109]. Recognizing the importance of patient perspectives, we propose aiming for a stakeholder target ratio of 1:1:2 (surgeons:other HCPs:people with DCM). The increased representation of people with DCM addresses their typically minor role in such studies and considers recent findings indicating a divergence in clinician- and patient-prioritized outcomes [4] and information needs [45]. This ratio also aligns with the status of people with DCM as the principal beneficiaries of the CIS and enhances its applicability from a patient and public perspective.

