For balanced geographical stakeholder representation, a 1:1:1 target ratio is proposed, spanning North America and Australasia; Europe and the United Kingdom; and “elsewhere,” comprising Africa and Asia. Including stakeholders from these regions will help ensure that the CIS considers a wide range of health care systems, cultural practices, and resource availability. However, it is worth noting that engaging participants from the “elsewhere” category may prove difficult. These regions, which are often underrepresented in the research community owing to fewer research resources and infrastructure [110], are similarly underrepresented in our specialized RECODE-DCM community. Recognizing this potential recruitment challenge upfront, we will aim to achieve equal regional representation during the final consensus meeting, with no items removed before this stage.

Carers (informal and formal) of people with DCM will also be invited to participate in the Delphi process as they offer significant practical and emotional support to people with DCM [16] and likely hold unique perspectives with regard to their information needs at the time of diagnosis. Consultation with informal carers, often subject to significant caregiving strain [16], may indirectly contribute to their welfare by promoting improved standards of care. However, we acknowledge that the recruitment of carers may be challenging as they are less likely to self-identify, as documented in related research domains [111]. In addition, the number of carers involved in the RECODE-DCM community is currently limited. For these reasons, no stakeholder or geographical target ratios will be specified for this group. Their involvement will be encouraged by existing HCPs and people with DCM in the community.

Participants will be invited to complete round 2 of the Delphi survey only if they have responded to round 1. A dropout rate of approximately 20% is expected from previous Delphi exercises [95,112]. Respondents who complete the Delphi process will be acknowledged in published material. No monetary incentives will be offered.

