#### Delphi Survey

An email campaign will be created in Gmail (Google) using a newsletter layout template and sent to HCPs, people with DCM, and carers in the contact directory of the RECODE-DCM network using the multisend function. The multisend option is a built-in mass-email feature that allows emails to be sent in bulk to distinct recipients, thus preserving their anonymity, which is a key feature of the Delphi method [98]. Participants will have the option to opt out of the process at any point through a unique “unsubscribe” link automatically added to each email. Recipients who unsubscribe will be removed from future email campaigns. The email will provide prospective Delphi panelists with a brief overview of the study. Potential panelists will be directed to Delphi round 1 via a SurveyMonkey web link embedded in a participation button at the bottom of the email. The survey will open to a short explanatory video and a web link to the Participant Information Sheet, which will provide a summary of the research project, aims, the inclusion and exclusion criteria, anonymity and confidentiality, and anticipated time commitment. The following biographical data will be collected for people with DCM: age, year of diagnosis, history of surgery or nonoperative management, and employment status. For HCPs, information about their profession, specialty, job title, and experience in managing DCM will be captured.

Panelists will be asked to independently rate the importance of information items using a 4-point Likert scale (“essential,” “very important,” “unimportant,” and “not at all important”). This range of response categories is more likely to produce stable findings in Delphi studies [95]. Respondents will also be asked to provide a brief rationale for their responses and whether the information items presented could be modified to improve their relevance using a comment box. It is common practice to include in questionnaires that respondents themselves complete an invitation to add issues not covered in the main part of the questionnaire or to expand on terms [123]. The presentation of information items will be randomized using a pseudorandom number generator throughout both rounds [124]. No more than 3 rounds will take place to ensure that the process does not become too repetitive and time-consuming to maintain an adequate response rate [80]. After each round, participants will be asked to read the feedback before responding again to statements.

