### Strengths and Limitations

The proposed study has several methodological strengths and limitations. First, the Delphi method offers an unbiased manner of soliciting consensus when this is lacking [174]. The guarantee of anonymity reduces expert-layperson power asymmetries between clinicians and patients, which are inherent in typical health care interactions [175]. This provision is particularly important to people with DCM, the beneficiaries of the CIS, to assert their viewpoints without reservation. Furthermore, the provision of systematic and controlled feedback fosters transparency, dialogue, learning, and sometimes novel insights that might not have been apparent in isolation [78]. Through its systematic progression, the Delphi method allows for gradual refinement of ideas [176]. Information items put forward for consensus in this manner are likely to become more patient-centric, relevant, and clear, ultimately resulting in the production of a more pertinent CIS. In addition, conducting the survey over the internet broadens the inclusion of people with DCM, including presurgical DCM, which is poorly represented in the conventional literature [50,177].

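### The draw for the deciding consensus meeting ignores treatment history, so no nonoperatively managed person may be present for the vote

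*Protocol article*

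**What the plan says.** All places are in the protocol article.

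- **Expert Selection** admits people with DCM by two routes: at least 6 months after decompressive surgery, or at least 6 months of nonoperative management. It sets no balance between them. The panel aims for a "stakeholder target ratio of 1:1:2 (surgeons:other HCPs:people with DCM"), so all people with DCM form one category. The only other balancing factor is region: "For balanced geographical stakeholder representation, a 1:1:1 target ratio is proposed". For carers, "no stakeholder or geographical target ratios will be specified for this group".
- **Delphi Survey** collects from people with DCM "age, year of diagnosis, history of surgery or nonoperative management, and employment status".
- **Consensus Meeting** caps attendance at 20 people, drawn at random from those who finished the two survey rounds. The draw has a single stated constraint: "preserving the key stakeholder and geographical representation previously described".
- **Consensus Criteria** applies the 75% thresholds only after the meeting. Under **Consensus Meeting**, an item split 50:50 is discussed and voted on again, and any other item short of 75% is dropped. No item is removed earlier, so this vote settles the content of the set.

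**The concern.** The set is meant for use at diagnosis, whatever treatment follows. The protocol treats operated and nonoperatively managed people as distinct enough to need separate eligibility routes, and it records which route each person came by. It then leaves that field out of the rule for choosing who votes.

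People who have had surgery look back on a different course. They might weigh items on monitoring, nonoperative management or the surgical decision differently. If every patient seat goes to someone who has been operated on, the other group has no vote at the step that counts.

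The protocol already uses this kind of safeguard elsewhere: it expects one region to be hard to recruit and responds by aiming for equal regional representation at the final meeting. No such step is taken for treatment history. The process map interviews admit only operated patients (Recruitment Strategy and Skills Training), so the Delphi exercise is the only new data collection in this protocol that is open to nonoperatively managed people.

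**Working it through.** The protocol gives no probability or seat count on this point, so there is no stated figure to reproduce.

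**Inputs**
- Meeting size: at most 20 (Consensus Meeting).
- Ratio 1:1:2 (Expert Selection). Twenty seats give 20 × 1/4 = 5 surgeons, 5 other HCPs and 20 × 2/4 = 10 people with DCM. If carers take some seats, about 8 is used (assumption).
- Share of nonoperatively managed people among completing patients: not given. Assumed range 8% to 30%.
- Number of completing patients, N: not given. Assumed 24 to 60. The protocol's minimum of 15 per category less about 20% dropout gives 15 × 0.8 = 12, which is treated separately.

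**Formula.** With K nonoperative people among N completers and n seats, P(none) = C(N−K, n) / C(N, n). For a very large pool with share p, P(none) = (1−p)^n.

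**Ten seats, finite pools**

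| Share | N, K | P(none) |
|---|---|---|
| 8% | 24, 2 | (14 × 13)/(24 × 23) = 0.330 |
| 10% | 40, 4 | 0.300 |
| 10% | 60, 6 | 0.317 |
| 21% | 24, 5 | 0.047 |
| 20% | 40, 8 | 0.076 |
| 20% | 60, 12 | 0.087 |
| 29% | 24, 7 | 0.010 |
| 30% | 60, 18 | 0.020 |

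**Ten seats, large pool:** 0.9^10 = 0.349; 0.8^10 = 0.107; 0.7^10 = 0.028.

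**Eight seats, large pool:** 0.9^8 = 0.430; 0.8^8 = 0.168; 0.7^8 = 0.058.

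**Minimum panel, 12 completers and 10 seats:** one nonoperative person, 2/12 = 0.167; two, (2 × 1)/(12 × 11) = 0.015.

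**Does regional stratification remove the risk?** Take 10 completing patients in each of three regions and patient seats split 3/3/4.
- One nonoperative person per region: 0.7 × 0.7 × 0.6 = 0.294. Unstratified, 3 of 30 gives 0.281.
- Two per region: (56/120)² × (70/210) = 0.073. Unstratified, 6 of 30 gives 0.065.

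In these examples, stratifying by region leaves the probability almost unchanged.

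**Weight of a seat.** Inclusion needs 0.75 × 20 = 15 votes, and one seat is 1/20 = 5 percentage points.

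**The case against.** Much of the case on the other side stands.

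- Nonoperatively managed people rate every item in both rounds and can give reasons. Their comments feed the summaries, no item is removed before the meeting, and round 2 results are shown there. A reader might infer that their views vanish without trace. They do not, although the planned feedback is aggregate and would not show them separately.
- A reader might infer a contradiction with Strengths and Limitations, which counts as a strength broader inclusion, "including presurgical DCM, which is poorly represented in the conventional literature". That sentence is about running the survey over the internet and promises nothing about the meeting. Presurgical is also not the same as nonoperatively managed. There is no contradiction.
- A reader might infer that items these patients need will be lost. The protocol does not show that the two patient groups rate items differently; the divergence it cites is between clinicians and patients. At a 10% share about one seat of ten is expected, which moves a tally by at most 5 points and matters only for items near the threshold.
- The patient seats are not wholly unstratified, since region is preserved.
- The share is unknown, and at 30% or more the risk is small.
- A table by treatment history is a detail that a condensed article may leave to a fuller document, so its absence is not an error.

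What remains is the draw rule. The article states it explicitly, and it names the factors to be preserved without treatment history among them.

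**Conclusion.** The point holds as a limited design weakness. As written, the draw can leave nonoperatively managed people without a vote at the only step that decides inclusion. With 10 patient seats the chance is about 30-33% in pools of 24 to 60 when 8-10% of completing patients are nonoperative (35% in a large pool), 5-9% at about 20% (11%), and about 1-3% at 30%. It rises if carers take patient seats.

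These figures rest on three assumptions: the full 20 seats are filled at 1:1:2, selection is random with respect to treatment history, and the share lies in the range shown. They give the chance of absence, not the chance that an item's outcome changes, which the protocol gives no basis to compute. The case for acting is that the safeguard costs little and the field is already collected, not that harm has been shown.

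**What to change.** In Consensus Meeting, add treatment history as a selection factor for the patient seats. Allocate in proportion to completers, with at least one nonoperatively managed person where completers allow, and let stakeholder type and region take priority. With 10 seats, proportional allocation means about 1 seat at a 10% share, 2 at 20% and 3 at 30%, so the group is not overweighted. The chance of none then falls to zero whenever such a completer is available and can be seated within the regional split. A fixed higher quota would be a poor choice: three seats could not be filled if only 2 of 24 completers were nonoperative.

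At the meeting, show for each item the round 2 percentage rating it essential or very important by treatment history, beside the pooled figure and with the counts.

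The cost is one sentence in the draw rule and one extra column. The downside is one more constraint on a small draw, and subgroup percentages that rest on few people and should be read as descriptive only.

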### Objective 1: To Enhance People With DCM’s Knowledge of the Condition—Developing the First CIS for Use in DCM at Diagnosis

#### Delphi Consensus Process Overview

The Delphi technique is a well-established method for achieving consensus among experts on a given topic [77]. It is particularly suited to contexts in which knowledge is ambiguous, empirical evidence is scarce, or priority setting is required [78]. In this procedure, a panel of preselected experts are engaged in a series of structured surveys. Each round incorporates controlled feedback, usually a blend of quantitative and qualitative data, the purpose of which is to foster insights from previous rounds, prompting reflection and the potential revision of viewpoints [79]. Designed to incrementally foster a convergence of opinions, the procedure is usually conducted anonymously, allowing participants to freely articulate their perspectives [80]. The number of rounds, execution of question delivery and response acquisition, and standards of achieving of “consensus” can vary within this general framework. Figure 1 provides a schematic overview of our approach, comprising 2 anonymized web-based surveys followed by a consensus meeting hosted over the internet. Consensus meetings offer a platform for real-time dialogue [81]. This face-to-face component has been observed to play a role in refining and enhancing the group’s collective understanding, paving the way for a more sophisticated consensus [82].

The Delphi method has been widely used in health sciences [83] to generate clinical recommendations [84] and standards and guidelines for theoretical or methodological issues [83,85,86] for a range of chronic illnesses such as diabetes [87,88], cancer [89,90], asthma [91], rheumatoid arthritis [92], and spinal cord injury [93,94]. Our objective using a Delphi procedure is to develop a CIS that facilitates optimal communication of information to people with DCM about the condition at the point of diagnosis. Figure 2 shows an overview of the phases involved in developing the CIS.

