##### Interrater Stability

Descriptive statistics reflect the level of overall consensus in a given sample but may not account for random change agreement and, therefore, may fail to accurately depict “true” consensus [130]. The κ statistic measures agreement beyond that expected by chance [130]. A weighted κ coefficient will be calculated after round 2 for the between-participant agreement on each information item. This variant is preferred compared with its unweighted equivalent as it is more suited to ordinal data given its ability to account for the magnitude of differences between the agreement levels [131]. The κ statistic will be particularly helpful for guiding the direction of conversations during the consensus meeting, ensuring that discussions are rooted in objective findings. κ calculations will be provided for each information item along with the reference value description of the agreement level in accordance with the study by McHugh [132] (Table 2).

No information items will be removed during these rounds. Data analyses will be conducted using SPSS (version 26; IBM Corp), and graphs will be produced using Microsoft Excel (Microsoft Corp).

**Table 2 table2:** Level of agreement represented by κ values^a^.

κ value	Agreement level
0.0-0.2	None
0.21-0.39	Minimal
0.40-0.59	Weak
0.60-0.79	Moderate
0.80-0.90	Strong
≥0.90	Almost perfect

^a^Adapted from the study by McHugh [132].

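### Except for items tied at exactly 50%, the deciding vote at the consensus meeting is cast before any live discussion the protocol describes, and it is not repeated

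*Protocol article*

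**What the plan says.** The Consensus Meeting section sets out the steps in order.

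1. At most 20 people who completed both survey rounds are shown the round 2 results.
2. They are "asked to anonymously rate the importance of each item for a final time using the polling tool".
3. "Frequency percentages will be generated in real time and presented to the voters on-screen to facilitate discussion".
4. "The facilitator will guide further discussion regarding any items garnering equal consensus (50%) between the agreement" and disagreement categories, "before asking participants to vote again".
5. "In all other cases, items failing to meet the predetermined ≥75% consensus score will be eliminated".

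Four other sections bear on this:

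- **Delphi Consensus Process Overview** justifies adding a meeting by the live exchange it allows, which is said to improve the group's shared understanding, "paving the way for a more sophisticated consensus".
- **Interrater Stability** says κ, computed after round 2, will help in "guiding the direction of conversations during the consensus meeting". It also says that no items are removed during the survey rounds.
- **Consensus Criteria** sets the threshold at ≥75% and applies it only after the meeting.
- **Qualitative Analysis** provides for an anonymous summary of panelists' remarks to be shown after each round.

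**The concern.** The percentages displayed in step 3 come from the poll in step 2, so the discussion they prompt must follow that poll. For an item not tied at 50%, no further ballot comes after that discussion. The section therefore does not deliver what the overview gives as the reason for meeting.

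The matter is important because no item is dropped earlier and the criteria wait until after the meeting. All 31 items listed under The Questionnaire are decided here, by a group of at most 20, and the result is the study's primary output. If live argument cannot reach the ballot, then for non-tied items the meeting acts as one more anonymous rating by a smaller group. This applies on both sides of the threshold. An item can be kept at 75% before an objection is voiced live, or lost at 70% before it is defended live.

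**Working it through.** The protocol states no figure on this point, so there is nothing to reproduce. The check has two parts.

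**Order of steps.** I looked for any text that places live discussion before the deciding rating.

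- Consensus Meeting: the only thing described before the rating is the presentation of round 2 results. The first mention of discussion comes with the display of the poll's own percentages.
- The same section gives tied items "further" discussion without using the word earlier except for the exchange prompted by those percentages, so this too follows the rating.
- Interrater Stability: κ exists before the meeting and is meant to steer its conversations, but the section does not say whether these come before or after the vote.
- Delphi Consensus Process Overview: states the purpose of the meeting, not the sequence.

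No section places discussion before the rating. The one route from discussion to a ballot is the exact tie.

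**How narrow that route is (illustration only).** Inputs from the protocol: a maximum of 20 voters, a ≥75% threshold, and a re-vote only at 50%. Assumptions: exactly 20 vote, votes are independent, and each voter favours the item with probability p. The documents do not give p, so a range is shown.

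- Inclusion needs 0.75 × 20 = 15 or more favourable votes.
- Consensus for exclusion needs 15 or more unfavourable votes, that is, 5 or fewer favourable.
- Counts of 6 to 14 are without consensus: 9 counts. Only 10 leads to discussion and a second vote. The other 8 (6–9 and 11–14, or 30–45% and 55–70%) are eliminated on the poll already cast.

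The probability of an exact tie is P(X = 10) = C(20,10) × p¹⁰ × (1 − p)¹⁰, with C(20,10) = 184,756.

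| True support p | P(tie) | P(included on this poll) | P(eliminated without re-vote) |
|---|---|---|---|
| 50% | 17.6% | 2.1% | 80.3% |
| 65% | 6.9% | 24.5% | 68.6% |
| 70% | 3.1% | 41.6% | 55.3% |

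At p = 75%, P(tie) = 184,756 × (0.75 × 0.25)¹⁰ = 1.0%.

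At p = 70%, the chance of finishing on 14 or 15 votes, the two counts either side of the cut, is 37%. This shows how close such items lie to the boundary, not that discussion would move them.

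With an odd number voting, for example 19 or 15, an exact tie is impossible. Since 20 is only a maximum, it could happen that no item receives a vote after discussion.

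**The case against.** Several points on the other side have force.

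- **Tied items are discussed and voted on again.** This is correct. A reader might infer that live dialogue can reach no vote at all. The documents do not support that, and the point is limited to non-tied items.
- **Reasons reach voters before the meeting.** Also correct. Panelists are asked for rationales in the survey, and summaries of others' remarks are shown after each round. A reader might infer that a patient's or clinician's reasons are first heard once an item has been decided. That goes too far: only the live exchange comes too late.
- **The article is condensed, and its mention of further discussion and of κ-guided conversation is compatible with discussion before the vote.** Compatible, but not stated. The article writes out a sequence, and that sequence has the rating first. If discussion first was intended, the section needs correcting.
- **If items are taken one at a time, discussion of one could inform votes on later, related items.** This is possible; the section does not say how items are taken. It would still not help the item under discussion.
- **Rating first protects independent judgement.** The Strengths and Limitations section relies on anonymity to offset power differences between clinicians and patients, and live discussion before a vote carries some risk of influence. But rounds 1 and 2 already collect independent ratings, and the deciding ballot would remain anonymous under the fix.
- **The tie probabilities measure the re-vote trigger.** They do. They show how seldom a vote follows discussion, not how many decisions discussion would change. Twelve of the 21 possible counts (0–5 and 15–20) already meet the protocol's own consensus definition, so counting all 21 equally would overstate the matter.

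A reader might also take the meeting to replace a third survey. The overview says only that two surveys are followed by a meeting.

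**Conclusion.** The point holds in this limited form. For every item not tied at exactly 50%, the described procedure fixes the outcome on a rating cast before any described live discussion of that item. The dialogue given as the reason for the meeting, and the conversations κ is meant to guide, then cannot change whether that item is kept or eliminated. This is a conflict between the stated purpose and the stated procedure, and it affects the poll that determines the primary output.

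The conclusion about sequence rests on the text alone. The illustration, with ties at 17.6% down to 1.0% as true support rises from 50% to 75%, rests on 20 independent voters and assumed support levels. The documents do not allow an estimate of how many of the 31 items would end differently if discussion came first.

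**What to change.** Reorder the Consensus Meeting section. Show the round 2 results and the comment summary, hold the facilitated discussion, then open the anonymous poll and apply the ≥75% rule to that post-discussion vote. Give discussion time first to items whose round 2 support lay near 75% or differed between stakeholder groups; the latter comparison is already planned under Consensus Criteria.

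Reconcile the description of the rating as final with the second vote for tied items. If the tie re-vote is kept, say that the last ballot taken is the one that counts.

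The cost is a short rewording of the protocol and of any facilitator's guide, with the same attendees and polling tool. The downsides are some extra meeting time and possible influence from vocal members, which keeping the poll anonymous limits.

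### At the consensus meeting only items split at exactly 50% get a second vote, so items closer to the 75% inclusion bar are eliminated while less supported ones are reconsidered

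*Protocol article*

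**What the plan says.** The Consensus Criteria section defines three outcomes.

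- Inclusion: "items rated as “essential” or “very important” by ≥75% will qualify for inclusion".
- Exclusion: "those judged as “unimportant” or “not at all important” by ≥75% will qualify for exclusion".
- Neither: "Items not fulfilling these criteria will be defined as not having reached a consensus".

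On timing, it adds: "Consensus criteria will be applied after the consensus meeting". It does not say what becomes of an item in the third group.

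The Consensus Meeting section supplies that. At most 20 people who completed both survey rounds rate every item one last time by anonymous poll, with percentages shown live. Where agreement and disagreement are equal, at 50%, the facilitator leads further discussion "before asking participants to vote again". Then comes the general rule: "In all other cases, items failing to meet the predetermined ≥75% consensus score will be eliminated".

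The Interrater Stability section states that no item is removed during the survey rounds, so all 31 items reach this vote.

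**The concern.** A tie is the natural point of doubt under a simple majority rule. Under a 75% rule it has no special standing: the items whose fate is least settled are those just short of 75%. The plan gives the second vote to the former and withholds it from the latter.

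Three things follow.

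- More support can lead to worse treatment.
- Whether the second vote is available at all depends on whether the number of votes cast is even.
- Items without consensus share the fate of items rejected by consensus, so the separate ≥75% exclusion threshold does not affect which items are in the final set.

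The core information set is the study's primary outcome, and this rule alone fixes its content. Once the meeting has closed, a vote that was not taken cannot be recovered from the data.

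**Working it through.** There is no stated figure to reproduce. The check is to enumerate the rule and then illustrate it.

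**Inputs from the article**
- Inclusion at ≥75% agreement and exclusion at ≥75% disagreement (Consensus Criteria).
- Re-vote at a 50% split, elimination of all other items below 75%, and at most 20 voters (Consensus Meeting).

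**Assumed inputs**
- Attendance of 15 to 19 as alternatives to 20.
- For the illustration only: independent votes and a true probability of agreement p.

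**Step 1: the rule with n = 20 votes.** Inclusion needs k ≥ 0.75 × 20 = 15 in agreement. Exclusion by consensus needs 20 − k ≥ 15, that is k ≤ 5.

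| Agreeing votes | Agreement | Criteria category | Fate at the meeting |
|---|---|---|---|
| 15–20 | 75–100% | include | included |
| 11–14 | 55–70% | no consensus | eliminated, no second vote |
| 10 | 50% | no consensus | further discussion and second vote |
| 6–9 | 30–45% | no consensus | eliminated, no second vote |
| 0–5 | 0–25% | exclude | eliminated |

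An item at 14 is 15 − 14 = 1 vote short and is dropped. An item at 10 is 15 − 10 = 5 votes short and is voted on again. Of the nine counts in the no-consensus range (6 to 14), one triggers the second vote.

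**Step 2: other numbers of votes cast.**

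| n | Include at k ≥ | Exclude at k ≤ | Re-vote at | No consensus, eliminated without a second vote |
|---|---|---|---|---|
| 19 | 15 | 4 | never | 5–14 |
| 18 | 14 | 4 | 9 | 5–8, 10–13 |
| 17 | 13 | 4 | never | 5–12 |
| 16 | 12 | 4 | 8 | 5–7, 9–11 |
| 15 | 12 | 3 | never | 4–11 |

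A 50% split needs k = n/2, which is not a whole number when n is odd.

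**Step 3: illustration with n = 20.** P(X = k) = C(20, k) p^k (1 − p)^(20 − k).

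| p | P(X ≥ 15), included | P(11–14) | P(X = 10), re-vote | P(6–9) |
|---|---|---|---|---|
| 0.60 | 0.126 | 0.630 | 0.117 | 0.126 |
| 0.70 | 0.416 | 0.536 | 0.031 | 0.017 |
| 0.75 | 0.617 | 0.369 | 0.010 | 0.004 |
| 0.80 | 0.804 | 0.193 | 0.002 | 0.001 |

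The 11–14 column mixes two things: the narrow trigger, and the chance error of any 75% cutoff with 20 voters. To separate them, take the share of no-consensus results that the trigger reaches:

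- p = 0.60: 0.117 / (0.630 + 0.117 + 0.126) = 0.117 / 0.873 = 13%.
- p = 0.70: 0.031 / (0.536 + 0.031 + 0.017) = 0.031 / 0.584 = 5%.

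**Step 4: the two sections side by side.** Consensus Criteria separates exclusion from no consensus and gives no fate for the latter. Consensus Meeting eliminates both, apart from ties. If the ≥75% exclusion threshold were deleted, the final set would be the same.

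**The case against.** The best defence is that the rule is a deliberate tie-break. Items will already have been rated in two rounds with feedback, the process is capped at three rounds to avoid repetition, and a core information set is meant to be short. A strict bar with few repeat polls fits that purpose. This stands as a defence of the 75% bar, which is not challenged here. It does not explain why the extra poll goes to items five votes short and not to those one vote short.

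A reader might infer that items at 55–70% are dropped undiscussed. The article does not support that. Live percentages are shown for every item to help discussion, the κ values are meant to steer the conversation, and the tie clause speaks of further discussion, which implies some came before. What is confined to tied items is the facilitator-guided further discussion and the second vote. Even so, without a second vote, general discussion after the poll cannot change the fate of a non-tied item.

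A reader might also infer that the two sections contradict each other. They do not: one names a category without giving its fate, and the other supplies it. Items without consensus would stay out of the set under the remedy below as well, so this part is mainly about reporting. Nothing in the article forbids listing them separately.

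The probabilities are also open to challenge. The article gives no support levels, and voters who see earlier results and live percentages are unlikely to vote independently. The 0.193 at 80% support would arise under any 75% cutoff with 20 voters. Finally, an odd attendance does not by itself rule out a tie, since one abstention makes the count even. The parity point therefore concerns votes cast on an item.

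**Conclusion.** The concern holds as a defect in the stated re-vote trigger. With 20 votes, one count in the no-consensus range (10) earns a second vote and the other eight (6–9 and 11–14) do not. With an odd number of votes cast, none does. These results follow from the text alone and need no probability assumption.

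The binomial figures are illustrative. They rest on 20 independent voters and assumed support, and they should not be read as the harm caused by the trigger. How many items would change fate under a wider re-vote depends on how far discussion moves votes, which the article gives no means to estimate.

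The collapse of no consensus into elimination is a lesser point: it makes the exclusion threshold inert for the final set and blurs a distinction worth reporting. The rule should be changed before the meeting, because it decides the primary output and the missing votes cannot be supplied later.

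**What to change.** In Consensus Meeting, replace the 50% trigger. Every item that meets neither ≥75% criterion at the first meeting vote, that is with more than 25% and less than 75% agreement among votes cast, receives facilitated discussion and one re-vote. With 20 votes this covers counts 6–14, and with 19 votes 5–14, so it works for odd and even numbers.

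After the re-vote, apply the thresholds in Consensus Criteria unchanged. State there that items still without consensus are left out of the core set and are reported separately from items excluded by consensus.

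The cost is about two sentences of text and a somewhat longer meeting, since several of the 31 items may need a second poll. No additional survey round is needed, and the 75% bar stays as it is.
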